### Recruitment {15}

All patients receiving OAT from included OAT outpatient clinics will be considered the reference target population. A clinically based annual health assessment will be accessible to all patients in the included OAT clinics. Participants will be informed about the trial and invited to participate. Study personnel provides an extended evaluation for those giving informed consent and fulfilling the study eligibility criteria.

## Assignment of interventions: allocation

### Sequence generation {16a}

We will use 1:1 randomization that will be electronically registered using a randomization algorithm made through Stata that is linked to an electronic number for each patient (linked to CheckWare).

### Concealment mechanism {16b}

After all eligibility criteria have been met and consent has been obtained, a unique patient identifier number will be entered into a randomization spreadsheet to determine which study arms the participant will receive.

### Implementation {16c}

To enroll and assign participants, research nurses will use a randomization algorithm created through Stata linked to a patient's electronic number.

## Assignment of interventions: blinding

### Who will be blinded {17a}

Blinding of patients is regarded as complex and infeasible. Patients will be informed of the follow-up they will receive, but not of other follow-up alternatives that are used or the exact hypotheses for the study. Outcomes assessors and analysts will be blinded.

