### Intervention {11a}

The intervention is a supervised group-based exercise intervention for 16 weeks, which includes two outdoor sessions per week. The workout consists of two parts, the first focusing on endurance and the second focusing on resistance training. Every workout follows the same structure and lasts for approximately 45 min. The exercise starts with roughly 15 min of endurance warm-up, followed by moderate to high-intensity running or walking intervals. Eight repetitions of 30 s uphill, and the participants can freely choose between running and walking. The preferred intensity of the intervals is > 13 on Borg-score 20, meaning at least moderate-intensity activity [24]. The participants will be guided in using the Borg scale to identify exercise intensity, and the perceived exertion will be measured at the end of the endurance section. The resistance training consists of four exercises focusing on strengthening the large muscle groups, including pectoralis major, rectus abdominis, quadriceps femoris, gluteus maximus, and latissimus dorsi. The strength-training program follows the same structure as the intervals, 30 s of active time and approximately 60 s of break, four rounds.

The intervention is based on the World Health Organization 2020 guidelines on physical activity [25], and national guidelines for chronic obstructive pulmonary disorder [26]. In addition, a clinical therapist panel and users with extensive experience in exercise as therapy for drug and mental health disorders from Stavanger and Haukeland University Hospitals provided feedback on the intervention. We drew upon the preliminary experiences of patients and research personnel from the pilot study as well. Clinical staff, research staff, and people with user experience will supervise the exercise sessions. The supervisors have been trained to carry out this exercise program, and the research team will provide weekly guidance to these supervisors. Research nurses will perform random checks throughout the intervention period using the Borg-scale 20 [24], to determine whether intervention sessions use the desired intensity, or if any adjustments are needed.

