### Outcomes measures {12}

The data collection will take place within the patient’s local OAT clinic and the research nurse will lead the collection. The nurse has training in performing these tests, both as part of the annual assessment and in the pilot study.

Primary outcome measure:

Psychological distressThe primary outcome is psychological distress 12–16 weeks after intervention initiation assessed with the Norwegian-validated translation of the ten-item version of the Hopkins Symptom Checklist (SCL-10) [27]. SCL-10 is a valid, reliable, relatively brief, and easy tool to implement for assessing psychological distress symptoms. SCL-10 will be evaluated with mean SCL-10 item score, and compared between the intervention and control arm.

Secondary outcome measures 12 to 16 weeks after intervention initiation:Physical functioning assessed with a 4-min step test measuring the number of steps climbed in the period [28].Physical activity assessed using the Norwegian-validated translation of the International Physical Activity Questionnaire (IPAQ) [29].Changes in fatigue will be assessed with the Fatigue Symptom Scale (FSS-3) [30].Changes in health-related quality of life assessed with EuroQoL EQ-5D-5L [31, 32] in addition to a self-reported question on happiness on a 0 to 10 scale.Changes in self-reported substance use will be assessed comparing change in overall substance use (using a semi-continuous substance use score from 0 to 1 including frequency of intake of several substances) by before intervention and in a 1-year follow-up visit [11].Adherence to OAT (as proportion in each arm who 1 year after initiation of the intervention is receiving OAT with active follow-up during last month).Biochemical indicators of inflammation (measured with C-reactive protein in serum and total leukocyte count in blood).◦ Sub-group (*n* = 60): IFN-gamma, IL-1beta, IL-1RA, IL-6, IL-8, IL-10, IL-17A, MCP-1, TNF-alfa measured in dried blood spots.

Baseline characteristics as predictors for degree of active participation in the physical activity interventions will be assessed.

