### Procedure for unblinding if needed {17b}

Not applicable. The research nurses know patient assignment.

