## Data collection and management

### Plans for assessment and collection of outcomes {18a}

In both control and intervention groups, the outcome measures will be collected in the OAT clinics through a structured interview and clinical assessments of the participants.

Research personnel with background as health professionals will perform the data collection. Data collection and follow-up will be given in line with Table 1 and Fig. 1.

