### Data management {19}

Research nurses will collect all data using electronic data collection software (Checkware®). This information will be stored on the University Hospital of Bergen’s secure servers. This study will collect clinical data from electronic medical records (DIPS®).

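### The protocol says outcome assessors are blinded, but the research nurses who know the allocation are the role that collects the interview and nurse-administered outcomes, including the primary SCL-10

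*Protocol article*

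**What the plan says.** The blinding section of the protocol article (item 17a) says that patients cannot feasibly be blinded and then states "Outcomes assessors and analysts will be blinded". The Discussion puts the same point more softly, as an aim, and offers it in reply to the admitted difficulty of complete blinding.

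The next item, 17b, states "The research nurses know patient assignment". It makes no exception by clinic, visit or participant.

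Other sections give that role these tasks:

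- **Allocation** (Implementation, 16c): "To enroll and assign participants, research nurses will use a randomization algorithm created through Stata linked to a patient's electronic number".
- **Intervention delivery** (Intervention, 11a): "Research nurses will perform random checks throughout the intervention period", to see whether sessions reach the desired intensity.
- **Outcome collection** (Outcomes measures, 12): "the research nurse will lead the collection".
- **Schedule** (Table 1): a research nurse assessment is marked at screening, end-assessment, post-assessment and annual follow-up, with SCL-10 at all four.
- **Data capture** (Data management, 19): "Research nurses will collect all data using electronic data collection software".

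On the mode of collection, item 18a says that "the outcome measures will be collected in the OAT clinics through a structured interview and clinical assessments of the participants".

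**The concern.** A reader of 17a would take the trial to have blinded outcome assessment. A reader of 17b together with the outcome, schedule and data sections would conclude that the people who ask the questions and run the step test know the arm. Both cannot be true of the same role.

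This matters because the primary outcome is a subjective symptom score obtained by interview from participants who know what follow-up they receive. If the interviewer also knows the arm, blinding protects neither side of the measurement. The 4-min step test depends on effort and is run by the same role. Blinded assessment is the main safeguard that the article claims against detection bias at the point of measurement. A trial report that carried the claim forward would misstate the risk of bias for the primary outcome.

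**Working it through.** **Step 1. Who knows the allocation?** Research nurses, by the plain statement in 17b. Their tasks make this unavoidable for the group as a whole: they run the allocation (16c) and attend exercise sessions to check intensity (11a). They also meet every day with the staff who follow participants up (item 5d).

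**Step 2. Who assesses the outcomes?** Research nurses: they lead collection (item 12), are named in Table 1 at all four assessment visits, and collect the data (item 19). Item 18a uses the broader term research personnel, but it refers back to Table 1, which names the research nurse.

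**Step 3. Is another assessor described?** No. No section identifies someone independent of randomisation and session checks who is unaware of allocation.

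**Step 4. Which outcomes are exposed?**

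| Outcome | How obtained | Open to assessor knowledge? |
|---|---|---|
| SCL-10 (primary), IPAQ, FSS-3, EQ-5D-5L | Interview | Yes |
| 4-min step test | Administered by research nurse | Yes, partly limited by standard instructions |
| C-reactive protein, leukocytes, cytokines | Laboratory | Little |
| OAT retention at one year | Receipt of treatment | Little |

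**Step 5. The planning figures.** The sample size section gives a control mean of 2.2, SD 0.8, a mean of 1.8 in active participants and 62.5% taking active part. The intention-to-treat difference is 0.625 × (2.2 − 1.8) = 0.25, hence the stated mean of 1.95. By the normal approximation:

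n per arm = 2 × (1.960 + 0.842)² × 0.8² / 0.25² ≈ 160.8, rounded up to 161 (322 in total).

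The t-test version gives 161.7, rounded up to 162 per arm. This is the stated 324, with power 80.1%. The sample size is sound and is not at issue.

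**Step 6. Illustration of sensitivity.** Suppose there is no true effect, but a systematic difference b in reported SCL-10 between arms. The bias sizes are assumptions; the document gives none.

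SE = 0.8 × √(2/162) = 0.8/9 = 0.0889

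Rejection probability = 1 − Φ(1.96 − b/SE) + Φ(−1.96 − b/SE)

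| Assumed b | b/SE | Two-sided rejection probability |
|---|---|---|
| 0 | 0 | 5% |
| 0.05 | 0.56 | 8.7% |
| 0.10 | 1.13 | 20.3% |
| 0.15 | 1.69 | 39.3% |

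Here b is the total reporting difference, from participant and interviewer together.

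**The case against.** The strongest reply is that the documents do not say the nurse who randomised a participant also assesses that participant. There are several research nurses across clinics, item 18a speaks generally of research personnel, and the Discussion mentions the outcome assessor and the data collectors separately in one sentence. A different, unaware person might do each assessment. This stands to the extent that such an arrangement cannot be ruled out. It does not remove the contradiction: 17b exempts no nurse, and no such assessor is identified.

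The article also contains mitigations. Patients are not told of the other follow-up alternatives or the exact hypotheses (17a). The Discussion admits that full blinding is hard to achieve and describes a strict test protocol with the same instructions for all. These measures reduce response and motivation effects, but they do not make the assessor blind.

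SCL-10 is reported by participants who know what follow-up they receive, which the article discloses. Blinded assessors would remove only part of any reporting bias, and the documents do not say how much. This stands, and it limits what the error rates in the working can show. Unblinded collection of patient-reported outcomes can also be acceptable in an exercise trial, provided it is disclosed. The fault here is the contrary statement.

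A reader might infer that every outcome is compromised or that the analysts are unblinded too. The documents support neither. The laboratory markers and OAT retention offer little route for assessor bias, and nothing in the article contradicts analyst blinding.

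**Conclusion.** The point holds as an internal contradiction on a stated design property. As the article describes the procedures, the interview and nurse-administered outcomes, including the primary one, are not assessed blind, and 17a says that they are. This rests on reading 17b as covering all research nurses, which is its plain wording, and on the absence of any other named assessor.

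The size of any resulting bias cannot be derived from the document. The figures of about 9%, 20% and 39% show only that a planned difference of 0.25 is sensitive to modest reporting differences. A reader might take them as the trial's actual false-positive rate or as the cost of unblinded assessors. They are neither, because the bias sizes are assumed and include participant bias that blinded assessors would not remove. The direction of any bias is plausible but not established. The sample size calculation is unaffected.

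**What to change.** Reconcile items 17a and 17b and the Discussion, in one of two ways:

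1. If existing assessors are independent of randomisation and session checks and unaware of allocation, name that role. State which visits and outcomes it covers, and amend 17b, the outcome section, Table 1 and the data management section to match.
2. Otherwise, withdraw the assessor-blinding claim. State that participants and the research nurses who collect outcomes are not blinded and that analysts are planned to be. Report this as a detection-bias limitation for the primary outcome, and carry the same wording into the trial report.

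The cost of the second route is a correction of wording and a less favourable risk-of-bias statement.

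The interview mode for SCL-10 should stay as it is. Recruitment began in April 2022 and was expected to finish in December 2023, so a switch to self-completion now would mix modes on the primary outcome within and between participants. The article also describes no participant entry into the data collection software. Swapping nurses between clinics would not clearly help either, because 17b does not exempt nurses from other clinics.

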### Procedure for unblinding if needed {17b}

Not applicable. The research nurses know patient assignment.

## Data collection and management

### Plans for assessment and collection of outcomes {18a}

In both control and intervention groups, the outcome measures will be collected in the OAT clinics through a structured interview and clinical assessments of the participants.

Research personnel with background as health professionals will perform the data collection. Data collection and follow-up will be given in line with Table 1 and Fig. 1.

**Fig. 1 Fig1:**
[figure not shown]
Illustrates the timing of the intervention and follow-up for the study. *Measurements are timed as indicated by the arrows

### Plans to promote participant retention and complete follow-up {18b}

We assume participants will form a positive group dynamic which will promote participant retention. Further, we assume the intervention will be experienced as useful, which will also contribute to participant retention. Participants will also receive weekly appointment reminders and follow-ups from the research and clinical staff.

### Data management {19}

Research nurses will collect all data using electronic data collection software (Checkware®). This information will be stored on the University Hospital of Bergen’s secure servers. This study will collect clinical data from electronic medical records (DIPS®).

### Confidentiality {27}

All personal data is stored on a secure, access-restricted research server. The senior investigators [name] and [name] will import data from the collection software (Checkware®) and from the electronic medical record to a common file using each participant’s Norwegian personal identification number. Each participant is then given a computer-generated identification number for further analysis. Only anonymized data will be published.

Research nurses use paper forms for collecting the data during the trial and before data is entered into the collection software. Appointments are made using the medical record system. The research nurses store all paper forms that may be connected to a participant in a locked file in a room with restricted access.

For documentation and follow-up purposes, person-linkable data will be stored until the end of the project on the 31st of December 2029, and then deleted.

### Plans for collection, laboratory evaluation, and storage of biological specimens for genetic or molecular analysis in this trial/future use {33}

Blood samples with biochemical indicators of inflammation (C-reactive protein and leukocyte count with differentials) will be drawn from each participant at screening and at the intervention end-assessment.

## Statistical methods

### Statistical methods for primary and secondary outcomes {20a}

A detailed plan/protocol for analysis will be developed before data export and analysis adhering to the SPIRIT guidelines. Analysis methods and presentation of results will follow the CONSORT guidelines [33–35]. All tests will be two-sided. Descriptive results and efficacy estimates will be presented with 95% confidence intervals, and the statistical significance is set at *p* < 0.05. Potential confounders may be considered for adjustment if they are imbalanced at baseline, with assumed meaningful differences. Missing data will be considered, and appropriate imputations based on pre-defined assumptions will be done when necessary, as described in a detailed analysis plan. Categorical variables will be summarized as percentages and continuous variables as medians with interquartile ranges or means with standard deviation for variables with a Gaussian distribution. The primary outcomes will be analyzed with generalized linear models, Gaussian distribution. The main analyses will be analyzed as intention-to-treat.

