### Participant timeline {13}

See Table 1: Flow chart of the study outlining follow-up visits and assessment at each visit.

**Table 1 Tab1:** Flow chart of the study outlining follow-up visits and assessments at each visit

	**Screening (research nurse)**	**Treatment follow-up week 0 to 16 (nurses/social workers)**	**Intervention end-assessment (12–16 weeks after initiation)**	**Intervention post-assessment (10–30 weeks after intervention) initiation)**	**Annual follow-up**
**Research nurse assessment**	X		X	X	X
- Informed consent	X				
- Eligibility assessment	X				
- Follow-up by OAT staff		X			
- Clinical assessment	X		X	X	X
Biochemical tests	X		X	X	X
Physical funct. (4-min step test)	X		X	X	X
Physical activity. (IPAQ)	X		X	X	X
Psychological distress (SCL-10)	X		X	X	X
Fatigue symptoms (FSS-3)	X		X	X	X
Quality of life EQ-5D-5L	X		X		X

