### Sample size {14}

Based on a cohort study in the same population [11], we assume that psychological distress assessed with a mean item score of SCL-10 score is 2.2 with a standard deviation of 0.8. To detect a reduction in psychological distress to a mean level of SCL-10 of 1.8 which is under the typically used threshold of 1.85 for substantial psychological distress [27], among participants taking active part in intervention and being evaluated among those randomized to intervention groups, with 62.5% of the participants randomized to the intervention assumed to take active part in intervention (i.e., a mean among those randomized to the intervention of 1.95), with 80% power a 1.1 intervention: control ratio, a two-sided test, and alpha (*α)* error of 5%. Based on these assumptions, 324 persons are required in total, including 162 persons in the intervention arm and 162 persons in the control arm (statistical power was calculated in Stata SE 17.0).

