### Methods in analysis to handle protocol non-adherence and any statistical methods to handle missing data {20c}

If any variables are missing of the primary outcome, they will be handled using an intention-to-treat strategy; the baseline value will be used.

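### The only covariate rule in the protocol adjusts for what looks imbalanced at baseline; it should be replaced by adjustment for baseline SCL-10, fixed in advance

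*Protocol article*

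**What the plan says.** Section {20a} of the protocol article gives the primary model as follows: "The primary outcomes will be analyzed with generalized linear models, Gaussian distribution". No covariate is listed. The only sentence on adjustment is that "Potential confounders may be considered for adjustment if they are imbalanced at baseline, with assumed meaningful differences". The section also defers detail: "A detailed plan/protocol for analysis will be developed before data export and analysis adhering to the SPIRIT guidelines".

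The outcome section {12} describes the primary comparison in these terms: "SCL-10 will be evaluated with mean SCL-10 item score, and compared between the intervention and control arm". Table 1, in section {13}, schedules SCL-10 at screening as well as at the end-assessment, so a baseline value is planned for every participant. Section {20c} gives that value one definite use: when the primary outcome is missing, "the baseline value will be used".

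The sample size section {14} assumes "a mean item score of SCL-10 score is 2.2 with a standard deviation of 0.8". The intervention-arm mean is 1.95 after allowing for 62.5% active participation. It arrives at 324 participants, 162 per arm. It gives no correlation between baseline and follow-up SCL-10.

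**The concern.** Under randomisation, any baseline difference between arms is due to chance. Whether to adjust for a variable should therefore depend on how well it predicts the outcome, and that can be judged before the trial. The quoted rule uses observed imbalance instead. Three consequences follow.

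- The set of covariates cannot be known until the arms have been compared at baseline. A later analysis plan that keeps this criterion can define a threshold, but it cannot say in advance which model will be fitted.
- A strong predictor that happens to be balanced is left out, and the precision it would bring is lost. Baseline SCL-10 is the obvious candidate for the primary outcome.
- The decision is optional and has no threshold, so more than one primary analysis can be defended once the data are in.

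At stake are the width of the confidence interval for the primary effect and confidence that its p-value comes from a model chosen beforehand.

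**Working it through.** **Inputs.** From section {14}: control mean 2.2, intervention mean 1.95, SD 0.8, two-sided alpha 5%, 162 per arm. The diluted mean checks: 0.625 × 1.8 + 0.375 × 2.2 = 1.95, so the difference is 0.25. The correlation r between baseline and follow-up SCL-10 is not in the protocol; 0.3 to 0.7 is assumed.

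**Step 1: the plan's own figure.** The standard error of the difference is 0.8 × √(2/162) = 0.0889. A two-sample t-test (noncentral t) then has 80.07% power at 162 per arm and 79.83% at 161. So 162 per arm is the smallest size reaching 80%, and 324 reproduces exactly as an unadjusted comparison.

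**Step 2: fixed adjustment for baseline.** The residual SD is 0.8 × √(1 − r²). The same power formula at 162 per arm gives:

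| Assumed r | Residual SD | Variance removed | Power for 0.25 |
|---|---|---|---|
| 0 | 0.800 | 0% | 80.1% |
| 0.3 | 0.763 | 9% | 83.6% |
| 0.4 | 0.733 | 16% | 86.4% |
| 0.5 | 0.693 | 25% | 89.9% |
| 0.6 | 0.640 | 36% | 93.9% |
| 0.7 | 0.571 | 49% | 97.5% |

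**Step 3: the imbalance rule itself.** The protocol gives no threshold, so two common triggers were simulated for baseline SCL-10 (20,000 trials per setting, 162 per arm, normal data): adjust only if the baseline test has p < 0.05, or only if the standardised baseline difference exceeds 0.1. A third line takes whichever of the adjusted and unadjusted models gives the smaller p-value.

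| Strategy | Type I error, r = 0.5 / 0.7 | Power, r = 0.5 / 0.7 |
|---|---|---|
| Never adjust | 4.9% / 5.0% | 79.7% / 80.0% |
| Adjust if baseline p < 0.05 | 4.2% / 3.6% | 80.9% / 82.0% |
| Adjust if standardised difference > 0.1 | 3.7% / 2.7% | 84.8% / 89.9% |
| Always adjust | 5.0% / 4.9% | 89.7% / 97.5% |
| Free choice of the smaller p | 7.3% / 8.2% | not comparable, since error is not controlled |

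**Why the mechanical triggers lose power.** The standardised baseline difference has standard error √(2/162) = 0.111. A threshold of 0.1 is 0.1/0.111 = 0.9 standard errors and is crossed in about 37% of trials; the p < 0.05 trigger fires in 5%. In all other trials the unadjusted test is used, with a standard error that still counts baseline variation which the trigger has just shown to be small. The test is then too cautious.

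**Gain from fixed adjustment over each trigger.** Against the 0.1 threshold: 89.7 − 84.8 = 4.9 points at r = 0.5 and 97.5 − 89.9 = 7.6 points at r = 0.7. Against the p < 0.05 trigger: 89.7 − 80.9 = 8.8 and 97.5 − 82.0 = 15.5 points.

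**The case against.** The strongest reply is that a reader might infer that the primary analysis compares raw follow-up means and throws the baseline away. The document says neither. A Gaussian generalised linear model can carry a baseline term, covariate lists usually belong in the analysis plan, and that plan is promised before data export. The baseline value is used for missing outcomes, and the imbalance rule could itself bring it into the model. The rule is also permissive and does not mention the primary model. Sizing on the raw SD is compatible with an adjusted analysis and is conservative. All of this stands, so the missing covariate list is not the point made here. What remains is the criterion that the article does state. Writing the plan early does not cure it, because the trigger is a feature of the collected data.

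A reader might also infer that the primary p-value is inflated. The simulation does not support that for a rule applied mechanically, which errs on the safe side. Inflation needs discretion in choosing the model. Section {17a} says analysts are blinded, which limits that. It does not exclude it, because a two-sided p-value can be compared across models with the arms only coded.

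Nor is 80% the right starting point under every reading of the rule. With the 0.1 threshold the gain from fixed adjustment is about 5 to 8 points, not 10 to 17.

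Finally, the word change in several secondary outcomes in section {12} mostly labels the outcome and need not specify a change-score analysis.

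**Conclusion.** The concern holds as one of precision and pre-specification. The stated rule selects covariates by a criterion that does not suit a randomised trial. Under either way of applying it, adjustment for baseline SCL-10 fixed in advance does better: it keeps type I error at 5% and gives more power than the mechanical triggers, and it removes the choice that could take type I error to 7% to 8%.

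The size depends on the assumed correlation. Power at 162 per arm would be about 84%, 86%, 90%, 94% and 98% for r of 0.3, 0.4, 0.5, 0.6 and 0.7. The comparators are 80% with no adjustment and about 81% to 90% under the two triggers at r of 0.5 to 0.7. These figures also assume normal data, the planned effect of 0.25 and complete outcomes.

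The documents do not support saying that the sample size is wrong, that an unadjusted analysis would be invalid, or that the protocol excludes baseline SCL-10 from the model.

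**What to change.** Delete the imbalance-triggered sentence in section {20a} and put this in its place, here and in the analysis plan:

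*The primary analysis is a Gaussian linear model of SCL-10 at the end-assessment on randomised arm, adjusted for baseline SCL-10. The model is fixed before unblinded data are seen. Continuous secondary outcomes with a baseline value are analysed in the same way, each with its own baseline. Any other covariates are used only in a labelled sensitivity analysis.*

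Site (Bergen or Stavanger) may be added to the fixed list, but this is optional, since section {16a} states no stratification. The cost is a few sentences. The baseline data are already scheduled and the sample size stays at 324.

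### Exercise is delivered in groups in one arm only, but neither the sample size nor the named primary model allows for correlation within those groups

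*Protocol article*

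**What the plan says.** The protocol article describes an individually randomised 1:1 parallel-group trial (Trial design {8}). Treatment in the exercise arm is collective: "The intervention is a supervised group-based exercise intervention for 16 weeks, which includes two outdoor sessions per week" (Intervention {11a}). Sessions are led by clinical staff, research staff and people with user experience. The comparison group is recruited from the same clinics and has standard treatment without the exercise offer (Explanation for choice of comparators {6b}). The retention section adds: "We assume participants will form a positive group dynamic which will promote participant retention" ({18b}).

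Sample size {14} sets out its inputs: "we assume that psychological distress assessed with a mean item score of SCL-10 score is 2.2 with a standard deviation of 0.8"; "with 62.5% of the participants randomized to the intervention assumed to take active part in intervention", giving "a mean among those randomized to the intervention of 1.95"; and "with 80% power a 1.1 intervention: control ratio, a two-sided test", at 5% alpha. The result is "324 persons are required in total, including 162 persons in the intervention arm and 162 persons in the control arm". The section contains no group size, ICC or design effect.

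For the analysis, section {20a} states: "The primary outcomes will be analyzed with generalized linear models, Gaussian distribution". The same section defers details to an analysis plan to be written before data export. Clustering by exercise group or supervisor is not mentioned anywhere in the article.

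**The concern.** Individual randomisation balances the arms at baseline. It does not remove correlation that arises afterwards, when people train together for 16 weeks with the same peers and the same supervisors. Here such correlation can arise through treatment in one arm only, which makes the design partially nested. A sample size and a model that treat all participants as independent set the within-group ICC to zero, which is the most favourable value.

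If the ICC is above zero, the variance of the exercise-arm mean is larger than the independent formula gives. The trial then has less power than stated, and an unadjusted interval for the primary treatment difference covers less often than 95%.

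**Working it through.** **Inputs from the protocol article (Sample size {14}).** Control mean 2.2, SD 0.8, active participation 62.5%, mean among active participants 1.8, two-sided alpha 0.05, 162 per arm. The ratio printed there as 1.1 is read as 1:1, as in Trial design {8} and as the equal arms show.

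**Step 1: reproduce 324.** The diluted intervention mean is 2.2 − 0.625 × 0.4 = 1.95, so the difference is 0.25. A two-sample t-test on independent observations has power 79.8% with 161 per arm and 80.07% with 162 per arm. So 162 is the smallest adequate arm and the total is 324, an exact match. The normal approximation gives 161 per arm (322 in total), and 80.3% power with 162. There is no allowance for clustering and no slack.

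**Step 2: allow for clustering in the exercise arm only.** Group size m and ICC are assumptions, because the article gives neither. Total SD stays at 0.8 in both arms, and f is the share of the exercise arm that is clustered.

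- Design effect: DE = 1 + f(m − 1)ICC, with f = 1 (all clustered) or f = 0.625 (only active participants, with m the number of active members per group).
- SE = 0.8 × √(DE/162 + 1/162). The independent SE is 0.8 × √(2/162) = 0.0889. The SE ratio is √((1 + DE)/2).
- Power = Φ(0.25/SE − 1.96).
- Level of the unadjusted test when group effects vary around a zero average = 2 × [1 − Φ(1.96/SE ratio)].
- Total N for 80% power = 2 × (0.8 × 2.8016/0.25)² × (1 + DE) = 2 × 80.37 × (1 + DE), rounded up per arm.

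Example with m = 8, ICC 0.05, f = 0.625: DE = 1 + 0.625 × 7 × 0.05 = 1.219; SE ratio = √(2.219/2) = 1.053; power = Φ(2.8125/1.053 − 1.96) = 76%; level = 2 × [1 − Φ(1.96/1.053)] = 6.3%.

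| m | ICC | Clustered | SE ratio | Power | Level | N for 80% |
|---|---|---|---|---|---|---|
| 5 | 0.01 | active only | 1.006 | 79.8% | 5.1% | 326 |
| 5 | 0.01 | all | 1.010 | 79.5% | 5.2% | 328 |
| 8 | 0.02 | active only | 1.022 | 78.6% | 5.5% | 336 |
| 8 | 0.02 | all | 1.034 | 77.6% | 5.8% | 344 |
| 8 | 0.05 | active only | 1.053 | 76.1% | 6.3% | 358 |
| 8 | 0.05 | all | 1.084 | 73.7% | 7.1% | 378 |
| 12 | 0.05 | active only | 1.083 | 73.8% | 7.0% | 378 |
| 12 | 0.05 | all | 1.129 | 70.2% | 8.3% | 410 |
| 8 | 0.10 | active only | 1.104 | 72.2% | 7.6% | 392 |
| 8 | 0.10 | all | 1.162 | 67.7% | 9.2% | 436 |

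The normal approximation ignores the loss of degrees of freedom from having few groups. With groups of 12 there would be 162/12 ≈ 14 groups, so a correctly adjusted test would have slightly less power than shown.

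**The case against.** **The analysis plan may deal with it.** Section {20a} defers the details, and the sentence on the model names a family and a distribution. A reader might infer that the trial will be analysed without regard to groups. The article does not show that, because a group term or robust variance could still be added. The point about intervals therefore holds only for the model as named. The power figure is different: it is fixed in section {14}, and a later analysis plan cannot restore it.

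**The ICC is unknown.** A reader might infer that intervals are certainly too narrow and power certainly overstated. Both need an ICC above zero. The article gives no ICC, group size or number of groups, and does not say whether membership is fixed or rolling. The retention section mentions a group dynamic, but as an aid to staying in the trial, so it makes shared influence plausible without showing that SCL-10 scores correlate. The programme is also standardised: one session structure, trained supervisors, weekly guidance and intensity checks. That may keep supervisor effects small. This objection stands, and it is why the conclusion is conditional.

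**Site and season.** One might count these as sources of clustering. Controls come from the same clinics, and nothing suggests that season is confined to one arm. Shared effects of this kind largely cancel in the treatment difference. Only peers and supervisors are specific to the exercise arm.

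**Type I error.** It is tempting to say that it exceeds 5%. If exercise affects nobody, group delivery creates no extra variance in the exercise arm and the unadjusted test keeps its level. Inflation requires groups that differ in effect while averaging zero.

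**Participation.** Those who never attend share no sessions. The rows for active participants only are therefore closer to the protocol's own 62.5% assumption, and they are the milder ones.

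**Baseline adjustment could win the power back.** Perhaps, but that depends on the correlation between baseline and follow-up SCL-10, which the article does not give. With groups of 8 and ICC 0.05 for all participants, the variance ratio is (1 + 1.35)/2 = 1.175, so the correlation would have to exceed √(1 − 1/1.175) ≈ 0.39.

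**Conclusion.** The point holds in conditional form. The sample size makes no allowance for clustering by exercise group, and the primary model as named has no term for it. Power of 80.07% at ICC = 0 leaves no margin, so any positive within-group correlation takes it below 80% and makes unadjusted intervals too narrow.

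The size is by assumption. For groups of 8, ICC 0.02 costs one to three percentage points of power (about 78–79%), and ICC 0.05 leaves about 76% if only active participants cluster or 74% if all do. Groups of 12 at ICC 0.05 leave about 74% or 70%. At ICC 0.01 with small groups the loss is under one point and of no practical importance. The levels of 6–8% in the ICC 0.05 rows apply only where group effects vary around a zero average. The documents do not support saying that intervals are too narrow or type I error inflated as a matter of fact.

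**What to change.** 1. Record the exercise group (clinic or training group) of each exercise-arm participant. State a rule for rolling membership and for those who never attend. The per-protocol analysis in {20b} already needs participation data, although the article does not say whether these identify the group.
2. In the analysis plan, before data export, specify for the primary outcome either a partially nested linear mixed model (random group effect in the exercise arm only, small-sample degrees of freedom such as Satterthwaite or Kenward-Roger) or a cluster-robust variance with a small-sample correction.
3. Restate section {14} as 80% power at ICC = 0, and show power over a plausible range of ICC and group size.

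The cost is a group identifier and a few sentences, and nothing changes for participants. If membership was rolling, or has to be reconstructed (recruitment was due to end in December 2023), the identifier will take more work. The downside is slightly wider intervals and a less favourable stated power.
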